## Abstract

**Background:**

Ovarian cancer (OC) is one of the most aggressive tumors requiring new therapeutic approaches. Immunotherapy represents an opportunity, but to date, OC patients do not appear to benefit from current protocols. A better understanding of the composition of the tumor microenvironment (TME), especially in its immune components, could unveil mechanisms of immune suppression in a useful way to predict response to therapies and develop new therapeutic approaches.

**Method:**

The MICO (tumor MICroenvironment of Ovarian cancer) study is a single‐center observational study. Starting from peritoneal biopsy of high‐grade serous ovarian carcinoma (HGSOC), the purpose of the MICO study is to generate tumor patient‐derived organoid (PDOs) cultures and evaluate the concordance between in vitro platinum‐based chemotherapy sensitivity and in vivo sensitivity. Simultaneously, we will characterize through multiparameter cytofluorimetric analysis the composition of the OC TME, focusing on B lymphocytes and mast cells whose roles in ovarian cancer remain controversial and underinvestigated. Furthermore, patients experiencing recurrence will be longitudinally followed to monitor changes in the TME composition and the responsiveness of PDOs to in vitro stimulation with drugs.

**Discussion:**

The association between the composition of the TME, the reactivity of the PDOs, and patients' disease progression will be analyzed to identify whether specific subpopulations of tumor‐infiltrating immune cells could be predictive factors of the disease outcomes. The comparison of molecular profiles, in vitro response to drugs, and clinical‐pathological data will allow the definition of a pattern capable of predicting the response of the primary tumor for the identification of those patients who may benefit from specific treatment.

**Strengths and Limitations:**

The results of our study could help to better understand the OC behavior, may have implications for the development of effective immunotherapy and targeted pharmacological therapies for epithelial OC in a personalized medicine perspective. This will be a monocentric trial with an involvement of only 43 patients, so further studies will need to confirm our results.

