### Study Objectives and Endpoints

2.3

The primary endpoint of the MICO study will be to evaluate the concordance between in vitro platinum‐based chemotherapy sensitivity and in vivo sensitivity.

In more detail:
Organoids generation in vitro system to evaluate tumoral cells' response to carboplatin treatment.Patient's clinical response monitoring. We will record platinum‐free interval (defined as interval expressed in months between the last dose of platinum‐based chemotherapy and the recurrence or progression of the disease), progression‐free survival (calculated from the first surgery until the first disease progression or the last follow‐up) and overall survival (defined as the length of time from the date of first surgery to death or the date last seen). The disease recurrence or progression will be evaluated according to RECIST1.1 [32]. Relapsed patients will be divided according to response to platinum treatment as resistant (platinum‐free interval 1–6 months of last platinum cycle) and partially platinum‐sensitive/platinum‐sensitive (platinum‐free interval > 12 months).

The model will be considered concordant if PDOs of platinum‐resistant patients will be viable on day 5 after carboplatin addition and if PDOs of platinum‐sensitive/partially platinum‐sensitive patients will not be viable (see Section 2.8).

The secondary endpoints will be:
Characterize the composition of the immune TME in order to understand if there are differences between tumor‐infiltrating immune subpopulations among patients, differences that could be predictive of early recurrence and/or different responses to therapy, focusing on immune populations still poorly studied (such as B cells for acquired immunity and mast cells for innate immunity).Organoids generation in vitro system to evaluate tumoral cells' viability in response to PARP‐I treatment.Association of TME composition, organoid response to drugs, and clinical evidence to identify predictors of response to therapy.To compare the TME of HGSOC patients with the TME of the control group.To develop a platform that allows in vitro analysis of the tumor followed by the identification of personalized therapy for each patient and, in case of recurrence, to monitor over time changes in the composition and responsiveness of the patient's TME.

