### Sample Size

2.4

The sample size was calculated in order to evaluate the concordance between in vitro platinum‐based chemotherapy sensitivity and in vivo sensitivity.

From literature, this concordance is 0.80 with traditional patient‐derived xenografts [33]; we expect a concordance of 0.95 using PDOs [34]. A sample size of 93 patients will allow us to detect a true value of Cohen's Kappa of 0.95, with a power of 80% and an allocation of the two groups of 1:1.

Ninety‐three control patients will also be enrolled to compare the number of CD45+ cells at baseline. This sample size will allow estimating an effect size of CD45+ cell number of less than 0.3 between the control and case groups, with an alpha of 5% and power of 80%.

[32, 33].

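### The abstract gives 43 patients and Section 2.4 gives 93 for the same trial; 43 would have about 27% power, not 80%, for the stated kappa target, and the scale of the 0.80 benchmark is not stated

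*Protocol article*

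**What the plan says.** The abstract, under Strengths and Limitations, states "This will be a monocentric trial with an involvement of only 43 patients" and uses that small number as the reason why further studies will be needed.

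Section 2.4 (Sample Size) sizes the study on the primary endpoint, the concordance between platinum sensitivity of the organoids and of the patient. The benchmark is a published concordance of 0.80 for xenograft models. For organoids the authors write "we expect a concordance of 0.95 using PDOs". The number of cases is then justified in one sentence, which opens "A sample size of 93 patients will allow us to detect a true value of Cohen's Kappa of 0.95" and goes on to set power at 80% with two groups of equal size. A further 93 controls are planned for a comparison of CD45+ cells.

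The kappa sentence gives neither a null value nor an alpha. Section 2.11 (Statistical Methods) sets a two-tailed level of 0.05 for all tests.

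**The concern.** The two statements are both current text in one article, and they differ by a factor of more than two on the number of cases. The figure 43 appears once. It is not tied to an interim look, an evaluable subset, a subgroup or one of the two response groups. A reader cannot tell whether the abstract misdescribes the study or Section 2.4 sets a number that will not be recruited. If recruitment stopped at 43, the 80% power stated for the primary endpoint would not apply.

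A second, smaller point sits in the same paragraph. Both 0.80 and 0.95 are introduced as concordance, but only 0.95 is then called a kappa. Beating 80% raw agreement and beating a kappa of 0.80 are different tasks, and they need different numbers of patients.

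**Working it through.** **Inputs**
- Null 0.80 and alternative 0.95: Section 2.4. Reading 0.80 as the null kappa is an assumption, taken from the sentence before the kappa sentence.
- Power 80% and 1:1 split: Section 2.4. I take the split to mean that half the patients are resistant and half sensitive, so both margins of the 2×2 table are 0.5.
- Two-sided alpha 0.05: Section 2.11, an assumption for this calculation.

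**Step 1: reproduce the 93.** With both margins 0.5, the large-sample variance of kappa is (1 − κ²)/n. The standard deviation terms are √(1 − 0.80²) = 0.600 under the null and √(1 − 0.95²) = 0.312 under the alternative.

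n = [(1.960 × 0.600 + 0.842 × 0.312) / (0.95 − 0.80)]² = (1.4388 / 0.15)² = 92.003, rounded up to 93.

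This is the plan's figure. The other variants tried do not return it:

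| Variant | n |
|---|---|
| One-sided | 70 |
| Null variance only, two-sided | 126 |
| Null variance only, one-sided | 99 |
| Alternative variance only, two-sided | 35 |

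**Step 2: power from the same formula.** Power = Φ[(0.15√n − 1.960 × 0.600) / 0.312].
- n = 93: (1.4465 − 1.1760) / 0.3122 = 0.867, so power is 80.7%.
- n = 43: (0.9836 − 1.1760) / 0.3122 = −0.616, so power is 26.9%.

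**Step 3: does the method matter at n = 43?**
- Exact test on the equivalent agreement scale (κ = 0.80 is 90% agreement at a 1:1 split, κ = 0.95 is 97.5%): all 43 of 43 must agree, and power is 0.975⁴³ = 33.7%.
- Simulation with the null standard error: 33%. Normal formula with null variance only: 37%. Simulation with an empirical critical value: 38%.
- One-sided tests do better but still miss 80%: 50% by the formula and 68% by simulation.
- Using only the alternative variance gives 88%, but that test does not hold its level. Its critical distance is 1.960 × 0.312 / 0.600 = 1.02 null standard errors, an upper-tail error of about 15% instead of 2.5%. It also does not reproduce 93.

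**Step 4: is 43 a per-group count?** Two groups of 43 make 86, not 93, and 86 patients give 75.5% power by the Step 2 formula.

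**Step 5: the scale.** At a 1:1 split κ = (agreement − 0.5)/0.5. Raw agreement of 0.80 and 0.95 therefore corresponds to kappa of 0.60 and 0.90. If both figures were raw agreement, the one-sample formula would be

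n = [(1.960 × √(0.80 × 0.20) + 0.842 × √(0.95 × 0.05)) / 0.15]² = (0.9674 / 0.15)² = 41.6, rounded up to 42.

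For that target, 43 patients would have 83.3% power by an exact binomial test (at least 40 of 43 agreeing).

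**The case against.** The strongest reply is that Section 2.4 is the operative section. It names the statistic, power and split, and its 93 reproduces. The 43 is one number in a limitations sentence and may be a typing slip or a leftover. That is fair. It means the sample size calculation is coherent on the kappa scale and that the abstract is the likelier place for the error. It does not remove the contradiction, because nothing in the article says which number governs.

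The reply also rightly limits what can be built on the mismatch. Three stronger readings are tempting, and the article supports none of them:
- *A reader might infer that 43 comes from a raw-agreement calculation.* The formula gives 42, other variants give 32, 38, 44 and 49, and the article never explains the 43. The closeness may be chance.
- *A reader might infer that Section 2.3 sets a rival measure to kappa.* The sentence beginning "The model will be considered concordant if PDOs of" says which organoid and patient results count as agreeing. It defines the cells of the 2×2 table, from which kappa is also computed.
- *A reader might infer that concordance will be judged by a chi-square or Fisher test, since Section 2.11 names no agreement statistic.* That section assigns those tests to distributions across subgroups. A condensed article may leave the kappa analysis to the full protocol or SAP, so its absence is not a fault.

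**Conclusion.** The concern holds as a contradiction in the primary endpoint's sample size: 43 patients in the abstract against 93 cases plus 93 controls in Section 2.4. It must be corrected.

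Power at 43 for kappa 0.95 against 0.80 is about 27% by the formula that yields 93, and roughly 27% to 38% across the two-sided methods that take account of variability under the null. This rests on a null kappa of 0.80, two-sided 5% and margins of 0.5. The first two are not stated in the kappa sentence, though the reproduction of 93 supports them. The shortfall matters only if 43 is the real target.

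It would go too far to say that the planned power is unknown: Section 2.4 states it, and it checks. What is unclear there is the scale of the 0.80 benchmark, which the article alone cannot settle.

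**What to change.** - State one patient number in the abstract and in Section 2.4. If 93 stands, the abstract should read 93 cases plus 93 controls.
- In Section 2.4, state the null value, whether 0.80 and 0.95 are kappa or raw agreement, and the alpha with its sidedness.
- If 43 is the real number, withdraw the claim of 80% power for kappa 0.95 and report the power that 43 delivers, with the method used.

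The cost is a few words in the abstract and Section 2.4. No new data are needed, and no new calculation unless the answer is 43 or the benchmark proves to be raw agreement.

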**Trial Registration:**

The clinical trial has been registered at Clinical‐Trials.gov with the identifier NCT06272240 on 02/14/2024

AbbreviationsBMIbody mass indexCRSchemotherapy response scoreHGSOChigh grade serous ovarian carcinomaIDSinterval debulking surgeryMCsmast cellsNACTneoadjuvant chemotherapyOCovarian cancerPARP‐IPARP‐inhibitorsPBMCsperipheral blood mononucleated cellsPDOspatient‐derived organoidPDSprimary debulking surgeryPDXpatient‐derived xenograftsPIpredictive indexTILtumor‐infiltrating lymphocytesTMEtumor microenvironment

## Introduction

1

Despite the significant advances made by modern oncology, ovarian cancer (OC) remains one of the most aggressive tumors requiring new therapeutic approaches. The mechanisms underlying the development of OC are complex and heterogeneous and exhibit diverse features depending on the patient. A detailed understanding of these molecular mechanisms is essential for the development of innovative therapies tailored to the specific patient.

Over the past decades, advances in molecular and cellular biology have provided remarkable insights into the intricate dynamics underlying OC progression, revealing the pivotal role of the tumor microenvironment (TME) in shaping disease outcomes. TME is composed of a multi‐faceted assembly of stromal cells, immune cells, fibroblasts, blood vessels, and extracellular matrix components that together create a nurturing niche for tumor cells to thrive [1, 2, 3]. TME is also an attractive niche for microbial growth, and recently, it has been assumed that intra‐tumoral microbiota play a crucial role in shaping the TME in several tumors, including OC [4]. Among the components of the TME, immune infiltrate has garnered increasing attention due to its multifunctional roles in influencing tumor growth, metastasis, and therapeutic responses. It includes T, B, and natural killer cells, but also macrophages, dendritic cells, and mast cells that can take part in the orchestration of both the immune response against the tumor and the tumor's evasion mechanisms [5]. The immunosuppressive factors secreted by tumor cells, coupled with the recruitment of regulatory immune cells, contribute to the establishment of a microenvironment that hampers effective anti‐tumor immune responses. Conversely, mounting evidence suggests that a robust and well‐coordinated immune response can restrain tumor growth and metastasis development, highlighting the potential of immune‐based therapies in improving clinical outcomes for different cancer types, including OC [6, 7, 8, 9, 10, 11, 12, 13].

Lymphocytes are important components of the TME and include B and T cells. Indeed, multiple studies have shown that the presence of CD3^+^ and CD8^+^ tumor‐infiltrating lymphocytes (TIL) is associated with prolonged survival [6, 7, 8, 9, 10, 11, 12, 13]. Zhang et al. demonstrated that the presence of intratumoral T cells correlates with better clinical outcomes in advanced OC [14]. Depending on the degree of infiltration of T lymphocytes (CD3^+^ and CD8^+^) and using a standardized scoring system, tumors can be classified as “hot” or “cold.” “Hot” cancers exhibit high T cell infiltration, whereas “cold” tumors have few or none, or they are limited to the periphery of the tumor [15]. CD8^+^ TILs do not operate in isolation: tumors containing CD8^+^ TILs are often additionally infiltrated by CD20^+^ B cells, but their role in OC remains elusive [16]. Among the cells of the innate branch of the immune system present in the TME of OC, mast cells represent a controversial element, with authors supporting both anti‐tumoral and pro‐tumoral roles [17, 18]. A recent study showed that an abundance of naïve B cells and activated mast cells in the immune TME correlated with a worse prognosis [19]. Therefore, extensive knowledge of mast cells in OC is mandatory.

OC is a very heterogeneous tumor: the various shades of the TME composition, both between different OCs and within different sites of the same tumor, confirm it. In general, boosting the immune response against cancer cells represents a valuable therapeutic tool, but to date, OC patients do not appear to benefit from current immunotherapy protocols. We believe that deciphering the composition of the immune infiltrate in OC and pointing out the interplay among tumor and resident immune cells is necessary to better understand the behavior of OC.

Previous scientific studies have contributed to explaining the pathogenesis of OC using cell lines and animal models; however, the new frontier in biomedical research is represented by organoids, three‐dimensional cell culture systems obtained from a tissue fragment that reproduces the fundamental properties of the original tissue in vitro [20, 21, 22]. Cultures of epithelial organoids, which are found to be genetically and phenotypically stable when derived from both healthy and diseased tissues, can provide a valuable model for in vitro study of various pathologies [20]. They have paved the way for new large‐scale experimental techniques for the identification of genetic mutations that may provide specific sensitivities to anticancer drugs, thus enabling the definition of increasingly personalized treatments. Although organoid technology currently has some limitations, which can be attributed to some factors, including a lack of standardized protocols, heterogeneity amongst organoid preparations, and an absence of complexity and full physiological representation, (PDO) [23] have already found numerous applications in regenerative medicine and can be used to advance knowledge in the field of OC [24].

Starting from the patient's biopsy, the purpose of the MICO study (Study of the Role of the Tumor Microenvironment in Ovarian Cancer) is to characterize in detail the composition of the OC TME, focusing on B lymphocytes and mast cells that have been poorly investigated so far. Simultaneously, PDOs will be generated for each patient and will be employed for in vitro assays to evaluate the tumor's resistance to chemotherapy and to PARP inhibitors (PARP‐I). Furthermore, patients experiencing recurrence will be longitudinally followed to monitor changes in the TME composition and the responsiveness of PDOs to in vitro treatment with drugs. The association between the composition of the TME, the reactivity of the PDOs, and the survival rate of the patients will be analyzed in order to identify whether specific subpopulations of tumor‐infiltrating immune cells are predictive factors of the disease outcome. Finally, PDOs will be stored and used in the future for in vitro studies to find possible interactions among tumor cells and immune cells.

The comparison of molecular profiles, in vitro response to drugs, and clinical‐pathological data will allow the definition of patterns capable of predicting the response of the primary tumor for the identification of those patients who may benefit from treatment.

## Methods

2

### Trial Design

2.1

The MICO trial is a prospective monocentric study conducted at the University of Udine, Italy. Ethical approval was obtained from the Ethics Committee (CEUR FVG n. 17 380).

The MICO trial was registered on ClinicalTrials.gov under NCT06272240 identifier on 02/14/2024. Patients with International Federation of Gynecology and Obstetrics (FIGO) stages III–IV HGSOC (epithelial high grade serous ovarian carcinoma) will be enrolled. Peritoneal biopsies will be collected at the time of surgery (*t* = 0), and fresh tissue samples will be sent to the Pathology Department. Tumor tissue will be obtained at the time of diagnosis before any other treatment (Figure 1).

**FIGURE 1 cnr270242-fig-0001:**
[figure not shown]
Flowchart of MICO trial. t is expressed in months. NACT = neoadjuvant chemotherapy; TME = tumor microenvironment.

Clinical data collection of HGSOC patients will include age, menopausal status, Body Mass Index (BMI), BRCA mutational status, history of breast cancer, preoperative CA125, type of surgery, predictive index (PI) score, 2014 FIGO stage [25] and residual tumor.

All HGSOC patients will be triaged for staging laparoscopy (LPS) to obtain a histological diagnosis and to provide tumor load assessment through the PI score. The intraoperative evaluation will consist of histological diagnosis of HGSOC at frozen section and verification of diffusion intras‐abdominal disease.

Patients with LPS‐PI < 10 will undergo open primary debulking surgery (PDS); if PI was ≥ 10, patients were referred to neoadjuvant chemotherapy [26, 27].

After 3–4 cycles of neoadjuvant chemotherapy (NACT), in the presence of reduced tumor load, patients will undergo interval debulking surgery (IDS). During IDS, peritoneal biopsies will be collected at the time of surgery (*t* = 3) and fresh tissue samples will be sent to the Department of Medicine, University of Udine.

The pathologist will evaluate the chemotherapy response score (CRS), a three‐level pathological response scoring system on omental specimens, which can predict prognostic outcomes in patients with advanced epithelial OC undergoing neoadjuvant chemotherapy [28, 29].

At *t* = 0 and *t* = 3, the removed tissue will be sent to the Pathology Department, where it will be selected by the pathologist, who will collect a fragment of tumor tissue and will divide it into three parts: one for the identification of cells composing the TME (through multiparameter cytofluorimetric analysis), one for histological diagnosis, and one for organoid generation.

Through multiparameter cytofluorimetric analysis we will determine the main immune cell populations that infiltrate the tumor and, in parallel, the detailed immunophenotype of tumor infiltrating B cells and in the peripheral blood will be determined. Three different panels of antibodies will be used: one to identify the main populations of immune cells (CD45^+^) including B lymphocytes (CD19^+^), T cells (CD3^+^), and mast cells (FceRI^+^/cKIT^+^) in the TME (Figure 2). The other two panels will be employed for the complete characterization of B cells in the TME and in peripheral blood (Figure 3). Both Ab combinations allow the identification of transitional B cells (CD19^+^ CD24^++^ CD38^++^ CD27^−^ IgD^+^ IgM^+^), naïve B cells (CD19^+^ CD24^+/low^ CD38^+/low^ CD27^−^ IgD^+^ IgM^+^), memory unswitched + pre‐switched B cells (CD19^+^ CD24^+^ CD38^−^ CD27^+^ IgD^−/lo^ IgM^+^), memory switched B cells (CD19^+^ CD24^+^ CD38^−^ CD27^+^ IgD^−^ IgM^−^), plasmablasts (CD19^+^ CD24^−^ CD38^++^ CD27^+^ IgD^−/^ IgM^−^), and Double Negative (DN) B cells (CD19^+^ CD27^−^ IgD^−^). Figures 2 and 3 show the gating strategy employed to identify the main populations of immune cells in the TME (Figure 2) and to identify the B subpopulations in the TME (Figure 3) applied to the same representative HGSOC patient, respectively. Moreover, the concomitant evaluation of the positivity to CD21 on B cell subpopulations present in the peritoneal biopsy will allow us to characterize the activation status of the B cell subpopulations in the TME [30]. While the activation status of circulating B cells will be evaluated through the staining of CD71, a valuable marker of peripheral B cells proliferation [31].

**FIGURE 2 cnr270242-fig-0002:**
[figure not shown]
Proposed gating strategies for the identification of B cells, T cells, and mast cells (MC) among the CD45+ cells infiltrating the TME. Cells will be selected in the FSC‐A versus SSC‐A plot, then only singlets (SSC‐H vs. SSC‐A), viable (negative for L/D in L/D vs. SSC‐A plot) and CD45^+^ cells (CD45 vs. SSC‐A) will be taken into consideration for the analysis. B cells (CD19^+^) will be estimated directly among CD45^+^ cells, while T cells (CD3^+^) will be selected in the CD19^−^ gate. Finally, MC (c‐kit^+^ FceR^+^) will be visualized from the CD3^−^ gate. B cells, T cells, and MC percentages will be calculated on CD45^+^ cells. The gating strategy will be manually drawn by an expert flow cytometrist and applied to all samples.

